**Fig. 1 Fig1:**
[figure not shown]
POP study stepped-wedge RCT design Legend: Schematic of the stepped-wedge RCT design. Each building will be randomized to one of 4 waves during which they will receive the 6-month technical assistance intervention. There is a 1-month break/buffer period between each wave to facilitate measurement (e.g., staff surveys and fidelity checklist completion) and preparation for the subsequent wave. Not shown in the figure is that formal measurement of sustainment will occur for each building in the 8th month following wave completion

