### Statistical analysis

To estimate effects of the intervention on the primary outcome, we will use a linear mixed model that incorporates both within- and between-cluster information and accounts for secular temporal trends. In particular, to assess the intervention effect, we will use a model with random site effects of the form: *Y*_it_ = μ + β_1_t + β_2_I_*it*_ + β_3_I_*it*_(*t* – s_*i*_) + b_*i*_ where *Y*_*it*_ is the fidelity checklist score in building *i* during period t, for t ∈ (0, 1, …, 4). Each period is 6 months; *t* = 0 is the first 6-month period. *I*_it_ is an indicator variable; I_*it*_ = 1 if building *i* has been assigned to implementation at period t and *I*_it_ = 0 otherwise. s is the period when implementation begins for building *i*. b_*i*_ is a random effect associated with each building *i* (the deviation of the intercept for the building from the overall intercept μ). Models will take into account a general time trend and allow for the intervention effects to grow over time following implementation. Models will be fit using the lme4 package using R software. Each hypothesis will be tested using a two-sided level of significance α = 0.05. Similar models will be used for analysis of the secondary implementation outcomes.

Implementation sustainment will be measured in the 8th month after the conclusion of each 6-month intervention wave. Paired-samples *t* tests will be used to compare each building’s fidelity scores at the end of its control period with scores during the sustainment period. For buildings assigned to early waves, there is also an opportunity to measure longer term (> 12 months) sustainment within the study measurement period.

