### Power and sample size

With 20 buildings participating in the study and 4 “steps” or waves in the stepped-wedge RCT (i.e., *n* = 100 observations over time across all buildings given 5 total time points per building), we will have at least 80% power to detect an increase of approximately two-thirds of a standard deviation (*d* = 0.69) or larger in the primary implementation outcome, a meaningful and feasible difference. This assumes a moderate correlation between scores for the same building at different time points (ICC = 0.5), reflecting stable differences among buildings. Even in the unlikely event that we do not retain 20 buildings in the study, with 16 buildings we would still have at least 80% power to detect an increase of about three-quarters of a standard deviation (*d* = 0.77) in the primary implementation outcome. To make these effect sizes more concrete, if the checklist score had a standard deviation of 8 and an average score of 15 under the control condition, the stepped-wedge design has 80% power to detect an increase of about 5 to 6 points on the checklist score (e.g., an increase from 15 to 20).

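### The primary model pairs a straight-line calendar trend with a growth term, so curvature in the secular trend can bias the growth estimate; fixed period effects prevent this at little cost to the level effect

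*Protocol article*

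**What the plan says.** The Statistical analysis section prints the primary model. After the overall intercept its terms are "β_1_t + β_2_I_*it*_ + β_3_I_*it*_(*t* – s_*i*_) + b_*i", with t running from 0 to 4. Calendar time therefore has a single slope, the intervention has an immediate shift β2 and a linear change with time since crossover β3, and each building has a random intercept. The text describes this as "Models will take into account a general time trend and allow for the intervention effects to grow over time following implementation". It adds that "Each hypothesis will be tested using a two-sided level of significance α = 0.05" and carries a similar form to the secondary implementation outcomes. It does not say whether β2 or β3 decides the primary question.

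On time it states "Each period is 6 months", whereas the Fig. 1 legend says "There is a 1-month break/buffer period between each wave". The Power and sample size section claims "at least 80% power to detect an increase of approximately two-thirds of a standard deviation (*d* = 0.69"), based on "n* = 100 observations over time across all buildings given 5 total time points per building" and an ICC of 0.5.

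**The concern.** A single slope fits the background exactly only if fidelity drifts in a straight line. Four 6-month waves with three 1-month gaps between them take 4 × 6 + 3 × 1 = 27 months. Over that time the background could step up once buildings have completed their first self-assessment, level off, or rise and fall back.

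The growth variable I(t - s) is zero before crossover and climbs afterwards, so summed over buildings it is itself curved in calendar time. When the model has no other term for curvature, part of any bend in the background is assigned to β3. The trial could then report that the effect builds or fades after crossover when only the background bent.

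**Working it through.** **Inputs.** 20 buildings, 4 waves of 5 (Randomization); 5 assessments, one before wave 1 and one as each wave ends (Primary outcome); ICC 0.5, 80% power (Power and sample size); two-sided α = 0.05 (Statistical analysis). Total SD is set to 1, so between-building variance τ² = 0.5 and residual variance σ² = 0.5. Coding assumed: t = 0 is the baseline assessment, s is the wave number, and t - s = 0 at a building's first post-wave assessment.

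**Step 1: reproduce the stated power.** For a random-intercept stepped wedge with period effects and one intervention term, with X the treatment indicator, I = 20 buildings and T = 5 assessments:

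Var = Iσ²(σ² + Tτ²) / [(IU - W)σ² + (U² + ITU - TW - IV)τ²]

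- U = ΣX = 5 × (4 + 3 + 2 + 1) = 50
- W = sum of squared period totals = 0 + 25 + 100 + 225 + 400 = 750
- V = sum of squared building totals = 5 × (16 + 9 + 4 + 1) = 150
- Numerator: 20 × 0.5 × 3 = 30
- Denominator: 250 × 0.5 + (2500 + 5000 - 3750 - 3000) × 0.5 = 125 + 375 = 500
- Var = 0.06, SE = 0.2449, detectable d = (1.960 + 0.842) × 0.2449 = 0.686

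With 16 buildings, Var = 0.06 × 20/16 = 0.075 and d = 0.767. Both agree with the stated 0.69 and 0.77. Linear time gives the same 0.686. With linear time and the growth term added, the detectable β2 is 0.692, so β2 is the term that corresponds to the stated effect size.

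**Step 2: bias under the printed model.** Take no true effect and a background curve f(t) shared by all buildings. The generalized least squares estimate then has expectation (X′V⁻¹X)⁻¹X′V⁻¹f, where X is now the full design matrix. The chance that the nominal 5% test of β3 rejects is Φ(-1.96 - m) + 1 - Φ(1.96 - m), with m = bias / SE and SE(β3) = 0.1316. The shapes and their 0.5 SD size are assumptions.

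| Background over t = 0..4 (SD) | Bias β2 | Bias β3 per period | β3 rejection |
|---|---|---|---|
| S-curve 0, .025, .25, .475, .5 | 0 | 0 | 5.0% |
| Quadratic rise to .5 | +0.01 | +0.04 | 6.0% |
| Plateau 0, .25, .5, .5, .5 | -0.016 | -0.065 | 7.8% |
| Early jump 0, .5, .5, .5, .5 | -0.022 | -0.087 | 10.1% |
| Late jump 0, 0, 0, 0, .5 | +0.022 | +0.087 | 10.1% |
| Rise and fall 0, .25, .5, .25, 0 | -0.033 | -0.130 | 16.7% |

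For rise and fall, m = -0.130 / 0.1316 = -0.99. The implied effect three periods after the first post-wave assessment is -0.033 + 3 × (-0.130) = -0.42 SD, or 0.42 × 8 = 3.4 points at the protocol's illustrative SD of 8.

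**Step 3: where the exposure comes from.** Without the growth term, linear time leaves β2 unbiased for every shape tried, so the combination of a straight trend and a growth term is the cause.

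**Step 4: uneven loss.** If two buildings are lost from each of waves 1 and 2 and none from waves 3 and 4, rise and fall biases β2 by -0.12 SD (rejection 7.3%). Losing one building per wave leaves it at -0.03.

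**Step 5: period effects instead of β1·t.** All the biases above become exactly zero.

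| 20 buildings, ICC 0.5 | Linear time | Period effects | Change |
|---|---|---|---|
| SE(β2) | 0.2471 | 0.2475 | +0.2% |
| Detectable β2 | 0.692 | 0.694 | |
| SE(β3) | 0.1316 | 0.1429 | +8.6% |
| Detectable β3 per period | 0.369 | 0.400 | |
| SE, mean effect over four exposure periods | 0.336 | 0.350 | +4.1% |

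**The case against.** A linear trend is a recognised, economical choice with 100 observations, and much of the case for keeping it stands.

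- A reader might infer that any non-linear background change ends up in the growth estimate. It does not: shapes antisymmetric about mid-trial give no bias in the complete design, and other shapes leak only in part.
- A reader might infer that the powered comparison is unsafe. With balanced retention β2 is almost untouched and the stated power is unaffected. The 0.12 SD figure needs a lopsided pattern of loss together with the worst shape tried, and the protocol calls failing to retain 20 buildings unlikely.
- The trend sizes are assumptions, and milder shapes give rejection rates of 6% to 8%. The -0.42 SD figure concerns only the five wave 1 buildings at the last assessment.
- A reader might infer that the sustainment conclusion is at risk from this bias. Sustainment has its own paired comparison and does not rest on β3.
- Period effects are not free for the parameter in question: the variance of β3 rises about 18% (1.086² = 1.18).

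What remains is that the protocol does not leave the time term open. It prints a straight line, treats growth as part of the intervention effect, and does not mark β3 as subsidiary.

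**Conclusion.** The point holds for the growth term. With a single calendar slope, secular curvature about mid-trial biases β3 in either direction, by 0 to 0.13 SD per period for the 0.5 SD trends tried, and raises its false-positive rate from 5% to as much as 17%. The level effect is essentially protected unless buildings are lost unevenly across waves.

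The figures rest on ICC 0.5, a shared background curve, no true effect, assumed trend shapes and sizes, and the coding given above. If exposure were counted from 1 instead of 0, the β3 results would not change, but the bias in β2 would become (β2 bias - β3 bias). For rise and fall that is -0.033 + 0.130 = about +0.10 SD. Under that coding the detectable β2 is 0.740, which does not match the stated 0.69.

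**What to change.** Replace β1·t with a fixed effect for each of the five assessment periods (four indicators, baseline as reference), keeping β2, β3 and the building intercept. Do the same in the similarly specified models for the secondary implementation outcomes.

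This removes bias from any secular trend common to all buildings. It also drops the equal-spacing assumption for calendar time, which matters slightly because the 1-month gaps make assessments not exactly 6 months apart. It does not do so for the growth term, which still counts exposure in equal steps.

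The cost is three more parameters and about 9% in the standard error of β3 (0.132 to 0.143). The standard error of β2 rises about 0.2% with all 20 buildings, or from 0.275 to 0.281 in the uneven-loss case. The constant-effect detectable difference stays at 0.686, so the stated d = 0.69 needs no revision.

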^b^Buildings in the final intervention wave (wave 4) will complete self-assessment surveys at one additional timepoint, to allow completion of a final fidelity checklist to assess sustainment for this wave

**Table 4 Tab4:** Exploratory effectiveness outcomes from tenant surveys

Outcome	Measure
Overdose	Self-reported non-fatal overdose [56] and details about the overdose
Overdose risk behaviors	9-item instrument based on past research [57], with added item on using drugs behind a locked door
Naloxone use	Current possession, carrying, knowledge of sources, motivation to carry
Overdose risk knowledge	Brief Opioid Overdose Knowledge (BOOK) Survey [51]
Motivation for treatment/risk reduction	Motivation to initiate MOUD, obtain SUD treatment, and change overdose risk behaviors, with scales measuring importance, readiness, and confidence for making a change
Stigma	Perceived Stigma Toward Substance Users Scale [52]
SUD treatment and treatment barriers	Self-reported receipt of and barriers to SUD treatment, including MOUD [58]
PSH building services	Degree of comfort discussing substance use with building staff; self-report of building services related to substance use and overdose prevention

*Legend*: Table shows exploratory effectiveness outcomes for the stepped-wedge cluster RCT. Exploratory outcomes encompass tenant-level substance use and overdose-related measures. All are assessed via surveys administered to each tenant immediately before and 12 months following the start of their building’s intervention wave

*PSH staff surveys* will be conducted at five timepoints for staff from all participating buildings: once before the first intervention wave begins, and once as each of the four waves ends. All PSH staff with tenant-facing, supervisory, or leadership roles will be invited via e-mail to complete surveys. Invitation emails will include a hyperlink to a secure online REDCap survey. Invitations to participate in surveys will be non-coercive; it will be made clear that there will be no negative ramifications for their employment if staff decline to participate. A consent document will be included for staff to review prior to deciding whether to participate. Survey content is described in Table 3. Surveys are anticipated to take less than 20 min to complete.

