*Medicaid data analysis* will use statewide Medicaid data to examine tenant-level effectiveness outcomes, as outlined in Table 3. Participating PSH buildings will provide investigators with PSH tenant identifying information. Investigators will use deterministic matching procedures to link this data with New York Medicaid data. After linkage, individual identifying information will be removed to create a de-identified Medicaid dataset for analysis; a building code will be retained and each tenant will be given a unique non-identifying study code to facilitate longitudinal analyses.

*PSH tenant surveys* will be used to examine exploratory effectiveness outcomes. These surveys will be administered twice for tenants of each participating building: immediately before that building’s intervention wave starts and approximately 12 months later. Paper surveys will be mailed to each tenant with a consent document, instructions for completion, and a self-addressed stamped return envelope. Tenants will also be offered the option to complete the survey by phone or online. Tenant surveys are anticipated to take approximately 30 min to complete. The study team will take multiple steps to increase survey participation rates, including explaining to tenants that the surveys are confidential and doing direct outreach in the PSH buildings. Survey content is described in Table 4.

Buildings participating in the study will complete agreements outlining provisions for data sharing (i.e., of staff and tenant contact information for survey distribution and tenant identifying information for linkage with Medicaid data) with the study team.

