Secondary effectiveness outcomes using Medicaid data and staff surveys will use generalized linear mixed models appropriate to each type of outcome (e.g., a Poisson model to compare visit rates). Health service use variables (e.g., ED visits) will be calculated as rates when appropriate (e.g., visits per study population per time period). For all secondary and exploratory analyses, we will examine the amount and type of missing data (e.g., missing at random or not at random) and implement appropriate statistical procedures for missing data as necessary. We will examine exploratory outcomes from tenant surveys using mixed-effects regression analysis. For the post-intervention survey time point we will conduct sub-analyses limited to tenants who have lived for at least 6 months in the building.

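### The tenant-survey sub-analysis limits only the post-intervention survey to tenants with at least 6 months' residence and names no matching pre-intervention group

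*Protocol article*

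**What the plan says.** The tenant surveys supply the exploratory effectiveness outcomes in Table 4: non-fatal overdose, risk behaviors, naloxone, knowledge, stigma, treatment and building services.

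- **Timing.** Each building is surveyed twice, "immediately before that building’s intervention wave starts and approximately 12 months later" (Secondary and exploratory outcomes). The Table 4 legend agrees: "All are assessed via surveys administered to each tenant immediately before and 12 months following the start of their building’s intervention wave".
- **Who is surveyed.** "Paper surveys will be mailed to each tenant with a consent document, instructions for completion, and a self-addressed stamped return envelope". No minimum residence is set for either mailing.
- **Main analysis.** "We will examine exploratory outcomes from tenant surveys using mixed-effects regression analysis" (Statistical analysis).
- **Sub-analysis.** The next sentence sets the limit and ties it to one survey: "For the post-intervention survey time point we will conduct sub-analyses limited to tenants who have lived for at least 6 months in the building".

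The article names no limit for the first survey, no adjustment for length of residence, and no other comparator for the restricted post-intervention group.

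**The concern.** If turnover is steady, surveying all tenants at both times gives a similar mix of new and established tenants before and after. Restricting the second survey alone removes that balance: the before group still contains people who moved in last month, and the after group contains nobody resident for less than 6 months. Any outcome that varies with time in the building would then shift between surveys even if the intervention did nothing.

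Several Table 4 outcomes could plausibly vary in this way. Knowing where to get naloxone, comfort in talking to building staff and awareness of building services may all build up with time in the building. At stake is whether this sub-analysis can be read as showing change associated with the intervention, or whether part of it reflects who was counted.

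**Working it through.** **Plan's own figures.** No figure in the article bears on this point. Its only power statement concerns the primary fidelity outcome: d = 0.69 with 20 buildings and 0.77 with 16, at ICC 0.5. A stepped-wedge variance calculation reproduces it (0.686 to 0.694 and 0.767 to 0.775). It does not enter what follows.

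**Who the limit removes.** The intervention lasts 6 months and the second survey falls about 12 months after its start. A tenant with under 6 months' residence at month 12 arrived after month 6, when the intervention had ended. A tenant continuously resident since the first survey has at least about 12 months' residence and is never removed. So the limit drops only later arrivals, who have no first-survey response. It does nothing to the equally new tenants who answered the first survey.

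**Size of the imbalance with no intervention effect.** Inputs:

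- q = share of respondents with under 6 months' residence, the same at both surveys. Not in the article; assumed 5% to 20%.
- m_L and m_N = outcome in longer-stay and newer tenants; delta = m_L − m_N. Not in the article; assumed 5 to 20 percentage points.

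Before, all tenants: q × m_N + (1 − q) × m_L.
After, limited: m_L.
Spurious change = m_L − [q × m_N + (1 − q) × m_L] = q × delta.

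| q | delta = 5 | delta = 10 | delta = 20 |
|---|---|---|---|
| 5% | 0.25 | 0.5 | 1 |
| 10% | 0.5 | 1 | 2 |
| 15% | 0.75 | 1.5 | 3 |
| 20% | 1 | 2 | 4 |

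(Percentage points. If newer tenants have the higher value, the sign reverses.)

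Example: outcome 40% in longer-stay tenants, 20% in newer ones, q = 10%. Before = 0.10 × 20 + 0.90 × 40 = 38%; after = 40%; spurious change +2 points. With the limit at both surveys it is 40% against 40%, so zero.

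**Is the range for q reasonable?** With constant annual turnover a, the share resident under 6 months is 1 − √(1 − a): 5.1% at a = 10%, 10.6% at 20%, 16.3% at 30%. Conversely, q = 20% needs a = 1 − 0.8² = 36%.

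**Calendar timing.** Six-month waves with 1-month buffers (Fig. 1 legend) start at about months 0, 7, 14 and 21, so pre-surveys fall there and post-surveys at months 12, 19, 26 and 33. The wave 1 post-survey (12) lies close to the wave 3 pre-survey (14), and the wave 2 post-survey (19) close to the wave 4 pre-survey (21). For waves 3 and 4 the nearest pre-survey is at month 21, which is 26 − 21 = 5 and 33 − 21 = 12 months earlier. Near-concurrent unexposed responses therefore exist for only two of the four waves.

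**The case against.** The strongest defence is that the limit defines exposure. It keeps out people who were not in the building during the intervention, and before the intervention nobody is exposed, so no limit is needed there. The first half stands: the limit has a sound purpose. The second half does not follow, because the before group has to stand in for what the after group would have looked like without the intervention, and a group that includes new arrivals does not do that for one that excludes them.

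Second, the article never says what the restricted group is compared with. This also stands. That it is all baseline tenants is an inference, though the natural one, since no other pre-intervention survey is described. The model's covariates and random effects may properly be set elsewhere; what the article does fix is a limit at one survey only.

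Third, tenants who answer both surveys are untouched by the limit, so the within-tenant information is sound in this respect. That is correct, and is why a within-tenant analysis belongs in the fix. It does not protect an analysis that also uses the one-time respondents.

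A reader might go further and infer that the sub-analysis would make overdose, risk behavior and naloxone possession appear to improve. Table 2 gives transitions as an example of higher-risk periods, and on a ratio scale the apparent reduction is 1 − 1/(1 − p + p × RR), with p the share of newer tenants and RR their relative risk: 4.8% at p = 10%, RR = 1.5; 16.7% at 20%, 2; 37.5% at 30%, 3. The arithmetic is right, but the article does not support the conclusion. It does not identify move-in as the transition meant, gives no p or RR, and says nothing about residence and naloxone possession or risk behavior. With RR = 0.5 and p = 20% the same formula gives 1 − 1/0.9 = −11.1%, an apparent increase. The top figure also needs 30% of respondents resident under 6 months, which implies annual turnover of 1 − 0.7² = 51%.

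**Conclusion.** The point holds in limited form. As written, the residency limit applies to one side of a before-after contrast, so length of residence differs between the sides by construction and could bias the result. Under the assumed ranges (5% to 20% newer tenants, a 5 to 20 point outcome difference, stable tenure mix, no true effect) the bias is about 0.25 to 4 percentage points. Its direction cannot be determined from the article, and the all-tenant comparator is an inference from the plain wording.

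The reach is small: one sub-analysis of exploratory outcomes. The all-tenant survey analysis will stand beside it. The fidelity outcome and the Medicaid outcomes do not use this rule. It is worth correcting because the correction is cheap, not because it threatens the trial's main conclusions.

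**What to change.** 1. Record length of residence, or move-in date, at both surveys. Settle this before the first survey goes out, since move-in dates of tenants who later leave are harder to recover.
2. In this sub-analysis, either apply the same at-least-6-months limit at both surveys or adjust for length of residence, and state which in the text.
3. Add a within-tenant analysis of those who answered both surveys. It keeps the people the same, although each has about 12 more months of residence at the second survey and those who left are not represented.
4. Secondarily, include survey calendar time in the mixed model, and note that near-concurrent pre-surveys exist only for the post-surveys of waves 1 and 2, so adjustment for waves 3 and 4 relies more on the modeled time trend.

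Cost: one extra field at the first survey and modest analysis work. A limit at both surveys shrinks the pre-survey sample. Applied separately at each survey, it also discards the first response of a tenant who was, say, 3 months in at baseline and is about 15 months in and fully exposed at follow-up. That breaks some pairs, so tenure adjustment or the within-tenant analysis should accompany it.
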